#### Secondary outcomes

Time to first exacerbation and hospitalisation will be assessed with Kaplan–Meier curves and Cox proportional hazard models. Dichotomous secondary outcomes will be analysed with logistic regression models and continuous secondary outcomes with analysis of covariance. All analyses will be adjusted for the variables included in the balancing algorithm for randomisation, i.e. study center, gender, age and current smoking. Because of the exploratory nature of the analyses, no correction will be made for the multiple analyses. All analyses of the trial will use the intention-to-treat population, defined as all randomly assigned participants who received at least 1 dose of study medication. A per-protocol analysis will be performed on those participants with a good compliance i.e. obtaining a serum 25(OH)D concentration above the 20^th^ percentile after 12 months. Also, a subgroup analysis will be performed in participants with a baseline serum 25(OH)D concentration of 25 nmol/L or less.

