## Outcomes

### Primary outcome

#### Exacerbation rate

Primary outcome is exacerbation rate. An exacerbation is defined as sustained worsening of respiratory symptoms during 48 h requiring oral corticosteroid, antibiotic or combination treatment that was initiated by a physician. Respiratory symptoms include at least one of the Anthonisen criteria, which are increased dyspnoea, sputum volume or sputum purulence, with or without minor symptoms such as cough, fever, common cold, wheezing or sore throat [38]. Participants will register symptoms and changes in medication on a diary card during the whole study period. During each telephone contact and study visit diary cards will be discussed and reviewed. Also questions will be asked regarding hospitalization during the last months. If necessary, information on changes in medication and COPD exacerbations during the study period will be confirmed through contact with the providing pharmacist, the general practitioner and hospital.

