#### Use of antibiotic and corticosteroids

With the use of earlier mentioned diary card and interviews the use of antibiotics and corticosteroids will be registered.

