### Sample size calculation

The study is designed to demonstrate a minimum difference of one exacerbation per patient-year between the vitamin D and the placebo group. We based our assumptions on post-hoc analyses of the RCT by Lehouck et al.[30], which had a similar patient sample, although without selection for vitamin D deficiency. Based on differences in Poisson means, a sample size of 94 participants per group is needed to demonstrate a difference of 1 exacerbation per patient-year with 80 % power at 5 % significance. This number was based on the assumption of 2.45 exacerbations per patient-year in the intervention group and 3.45 in the placebo group. To account for a dropout rate of 20 % 120 participants will be recruited per study group.

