### Statistical analysis

#### Primary outcome

The primary outcome of the trial, exacerbation rate, will be analysed with generalized linear models for a Poisson distribution. Analyses will be adjusted for the variables included in the balancing algorithm for randomisation, i.e. study center, gender, age and current smoking. The outcomes will be presented as rate ratios with their 95 % confidence interval.

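### Antibiotic and corticosteroid use accrues over the year, but the models named for secondary outcomes of this kind take no account of follow-up time

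*Protocol article*

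**What the plan says.** All references are to the protocol article.

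- **The outcome** (Outcomes, Use of antibiotic and corticosteroids): "With the use of earlier mentioned diary card and interviews the use of antibiotics and corticosteroids will be registered". Its form (any use, number of courses, days) is not given. The primary outcome section says of the same diary: "Participants will register symptoms and changes in medication on a diary card during the whole study period".
- **Models for secondary outcomes** (Statistical analysis, Secondary outcomes): "Time to first exacerbation and hospitalisation will be assessed with Kaplan–Meier curves and Cox proportional hazard models". All others are covered by "Dichotomous secondary outcomes will be analysed with logistic regression models and continuous secondary outcomes with analysis of covariance". The same section keeps every randomised participant with at least one dose in the analysis and describes the analyses as exploratory.
- **The primary outcome** (Statistical analysis, Primary outcome), drawn from the same diary, has a different model: "exacerbation rate, will be analysed with generalized linear models for a Poisson distribution", with results given as rate ratios.
- **Dropout** (Sample size calculation): "To account for a dropout rate of 20 % 120 participants will be recruited per study group".

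**The concern.** Drug use recorded over a year grows with time observed. A participant who leaves at month 3 without a course has not shown a year free of use, and a three-month count is not comparable with a twelve-month count. A logistic model of any use, or an ANCOVA of the amount used, treats the two alike. Keeping dropouts as observed ties the result to length of follow-up. Leaving them out turns the comparison into one of completers and departs from the stated analysis set.

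Two things are at stake: the size of the estimated effect, and protection against a false effect should the arms differ in dropout. A third arises only if use is reduced to yes/no. The exacerbation definition ("requiring oral corticosteroid, antibiotic or combination treatment that was initiated by a physician") ties every event to one of these drugs, so at the plan's rates nearly everyone would be a user and the yes/no form would discriminate poorly.

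**Working it through.** **Inputs from the article.** The sample size section gives the "assumption of 2.45 exacerbations per patient-year in the intervention group and 3.45 in the placebo group", 20% dropout and 120 recruited per group. Follow-up is one year.

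**Assumptions, not in the article.** Poisson counts; one course per exacerbation, varied to a half and a quarter; dropouts leave at a uniform time in the year; two-sided 5%; no covariate adjustment; any split of dropout by arm.

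**The plan's own figure.** The plain formula for a difference in Poisson means gives (1.960 + 0.842)² × (2.45 + 3.45) / 1² = 46.3, so 47 per group. The stated 94 per group is not reproduced; it would need a variance inflation of 94 / 46.3 = 2.03. The dropout step, 94 / 0.8 = 117.5, rounds up to 118, close to 120. This is a separate matter; only the rates, the 20% and the 120 are used below.

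**Step 1: equal dropout, counts.** Mean observed time is 0.8 × 1 + 0.2 × 0.5 = 0.90 year in both arms. Expected counts are 0.90 × 2.45 = 2.205 and 0.90 × 3.45 = 3.105. The difference is 0.90 in place of 1.00, a 10% attenuation. The rate ratio, 2.45 / 3.45 = 0.71, is unaffected.

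**Step 2: any use.** Over a full year P = 1 − exp(−rate): 0.914 and 0.968. For a dropout with a uniform leaving time P = 1 − [1 − exp(−rate)] / rate: 0.627 and 0.719. The gaps, 0.287 and 0.249, are the share of dropouts recorded as non-users who would have had a course by month 12: 0.287 × 24 = 6.9 and 0.249 × 24 = 6.0 people per arm.

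**Step 3: power by simulation** (120 per arm, 20% dropout in each).

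| Courses per exacerbation | Any use, yes/no | Mean count, no follow-up time | Rate with person-time |
|---|---|---|---|
| 1 | about 31% (30–33% depending on the test) | 97–98% | 99% |
| 1/2 | 47–48% | 82–83% | 86% |
| 1/4 | 39–40% | 55–56% | 57–58% |

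With gamma heterogeneity between patients (shape 2) and one course per exacerbation, the three figures are 26%, 75–77% and 79–81%.

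**Step 4: no true effect, 3.45 per year in both arms.** With 20% dropout in each arm, type I error in one simulation is 5.7% (yes/no), 4.9% (mean count) and 5.0% (rate).

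Now let dropout be 25% placebo and 15% vitamin D. Mean observed time is 0.875 and 0.925 year, so counts differ by 3.45 × 0.05 = 0.17 with no effect present. For any use, vitamin D has 0.85 × 0.968 + 0.15 × 0.719 = 0.931 and placebo 0.75 × 0.968 + 0.25 × 0.719 = 0.906, an odds ratio of about 1.4.

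| Dropout, placebo / vitamin D | Yes/no | Mean count | Rate |
|---|---|---|---|
| 25% / 15% | 8–11% | 11% | 5% |
| 30% / 10% | 24–31% | 28–29% | 5% |

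The range for yes/no reflects a Wald against a score test. The errors are smaller when courses are rarer: at a quarter of the rate the 25% / 15% split gives about 6% for both models.

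**The case against.** The strongest case against is that the article leaves the outcome's form open. It says only that use is registered, and the modelling sentence is conditional on whether an outcome is dichotomous or continuous; a count is strictly neither. A condensed article may leave this to the full protocol or analysis plan. Nor is the list of models evidently exhaustive: time to second exacerbation is a secondary outcome but is not named among the Cox analyses. The primary Poisson model states no offset either; person-time is only implied by the words rate and rate ratio.

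Much of this stands. A reader might infer that use will be dichotomised and most of the information lost. The article does not say so, and on the count route the power cost is only about 1–4 percentage points. Even with a yes/no coding, whether most information is lost depends on how often each drug is used: ignoring dropout, about 84% goes at the full exacerbation rates, but about 32% at a quarter of them. A reader might also infer that dropouts make the analysis invalid. With equal dropout they do not. The article gives one 20% figure and predicts no imbalance, and its provision to confirm medication changes with pharmacist, general practitioner and hospital may recover drug use for some who leave.

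What does not fall away is that the article states a modelling scheme for secondary outcomes, and neither route in it that drug use could take suits an outcome that accumulates over unequal follow-up. The primary outcome, from the same diary, has a model type that does.

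**Conclusion.** The point holds as a minor one. As written, drug use can be placed only under logistic regression or ANCOVA, and neither accounts for observation time.

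- **Equal dropout:** valid tests, with a mean difference in courses attenuated by about 10% if leaving times are uniform.
- **Unequal dropout (assumed, not predicted by the article):** a spurious effect is possible under both models. Type I error is about 8–11% at a 25% / 15% split and one course per exacerbation, against 5% for a rate.
- **Yes/no coding (not stated in the article):** a substantial loss of power, about 31% against 99% at one course per exacerbation, and 40% against 57% at a quarter of that.

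A rate with person-time did at least as well in every scenario tried, provided leaving is unrelated to the underlying rate of drug use. This is one secondary outcome among analyses called exploratory, and nothing here touches the primary result.

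**What to change.** In Statistical analysis, Secondary outcomes, add that the numbers of antibiotic courses and of oral corticosteroid courses per participant are each analysed as counts. Use the same type of model as the primary outcome, with the log of observed follow-up time as offset and adjustment for study center, gender, age and current smoking. Report rate ratios with 95% confidence intervals, and count each participant up to last contact. If a yes/no summary is wanted, use time to first course, censored at last contact, in place of a logistic model.

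The cost is a sentence or two. No new data should be needed, since the diary, telephone contacts and visits already cover the period. The only consequence is that results appear as rate ratios and not as odds ratios or mean differences.

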### Randomisation and masking

For treatment allocation in this trial, we will apply the sequential balancing method with study center as the first step in the balancing algorithm, followed by gender, age and current smoking. These variables are (potential) prognostic factors and thus should be balanced over the treatment arms. Pharmacists of the VU University Medical Center, who are independent from the clinical research team, will randomly assign participants by using a computer-generated randomisation list and will prepare the study medication. After the last participant finishes the trial masking will continue until after the data analyses.

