#### Spirometry measures

At t = 0 and t = 12 participants will undergo spirometry. The spirometry will be performed according to American Thoracic Society/European Respiratory Society (ATS/ERS) guidelines [39]. Only post-bronchodilator forced expiratory volume in one second (FEV_1_) and forced vital capacity (FVC) will be determined. Measurements will take place after inhalation of the sympathomimetic salbutamol and/or the anticholinergic ipratropium bromide. Inspiratory capacity (IC) and expiratory reserve volume (ERV) will also be determined according to ATS/ERS guidelines [39].

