#### Lung volumes

Measurements of absolute lung volume, residual volume (RV), functional residual capacity (FRC) and total lung capacity (TLC) will be assessed by body plethysmography according to guidelines of the ATS/ERS task force at t = 0 and t = 12 [40, 41].

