#### Physical performance

During every visit (t = 0, t = 6 and t = 12), participants will perform physical performance tests.

In the 6-min walking test the participant is asked to walk as far as possible during a period of 6 min. The participant will walk up and down a hallway. The 6-min walking test is performed according to the ATS guidelines [43].

In the chair-stands-test the participant will be asked to fold his arms across his chest and to stand up from a sitting position and sit down five times as quickly as possible [44, 45].

In the 3-meter walking test the participant is asked to walk three meters, turn around 180° and walk back [44, 46].

In the tandem test the participant is asked to stand with the heel of one foot directly in front of, and touching the toes of, the other foot for at least 20 s with his eyes open and closed [44, 47].

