#### Quality of life

Quality of life will be assessed by three questionnaires These will be completed at every study visit.

The St. George’s Respiratory Questionnaire (SGRQ) is designed to measure health impairment in patients with asthma and COPD [49, 50] and produces a symptoms score and an activity and impacts score.

The Short Form 12 health Survey (SF-12) is a multipurpose short-form generic measure of health status [51]. It is a validated subset of the larger SF-36 and monitors health in general and in specific populations. These scores correlate highly with the SF-36 versions [52]. The SF-12 has been previously used in patients with COPD [50, 53].

The Clinical COPD questionnaire (CCQ) is a simple 10-item, health-related quality of life questionnaire with good psychometric properties [54]. The questionnaire is responsive to pulmonary rehabilitation and a minimal clinically important difference has recently been defined [55].

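### The ANCOVA for continuous secondary outcomes names four adjustment variables but not the outcome's own baseline value, which costs precision if the text is followed literally

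*Protocol article*

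**What the plan says.** The Protocol article, Statistical analysis, Secondary outcomes, analyses "continuous secondary outcomes with analysis of covariance". Two sentences later it gives the adjustment rule for every secondary model: "All analyses will be adjusted for the variables included in the balancing algorithm for randomisation, i.e. study center, gender, age and current smoking". These four variables come from Randomisation and masking, which describes a "sequential balancing method with study center as the first step in the balancing algorithm, followed by gender, age and current smoking".

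The Outcomes section shows which continuous measures have a baseline value:

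- Spirometry: "At t = 0 and t = 12 participants will undergo spirometry".
- Lung volumes: body plethysmography "according to guidelines of the ATS/ERS task force at t = 0 and t = 12".
- Physical performance: "During every visit (t = 0, t = 6 and t = 12), participants will perform physical performance tests".
- Quality of life, three questionnaires: "These will be completed at every study visit". The two anxiety and depression scales follow the same schedule.
- Blood-cell substudy (50 participants): samples before and after the intervention.

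No visit times are given for grip strength, respiratory mouth pressures or the physical activity questionnaire in their own subsections. The article describes the secondary analyses as exploratory, without multiplicity correction.

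**The concern.** For a measure such as walking distance, FEV1 or a questionnaire score, the patient's own starting value is usually the strongest available predictor of the later value. Here it is collected, yet it is absent from the only list of covariates the article gives. An analyst working from that text could fit centre, gender, age and smoking, call the result an ANCOVA, and be fully compliant.

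Three features of the trial make this worth correcting:

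- The balancing factors contain no measure of lung function, exercise capacity or health status. A chance imbalance in these at baseline is therefore controlled neither by the allocation method nor by the model as written.
- The sample size is set for exacerbations alone, so precision for the continuous outcomes depends on the analysis model. The Introduction criticises an earlier study of physical performance for limited power and makes physical performance an additional aim of this trial.
- There are many such outcomes and no multiplicity control. If baseline is added only after the data are seen, it becomes an unplanned choice that can differ between outcomes.

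**Working it through.** **The plan's own figures.** The article gives no SD, target difference or power for any continuous outcome, so there is no stated figure to reproduce on this point. The only inputs taken from Sample size calculation are 120 recruited per group and 20% dropout: 120 × (1 − 0.20) = 96 completers per group. The 94 per group required for the primary outcome is not used.

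**Assumptions.** Two-sided 5% significance, 80% power and 1:1 allocation. The correlation ρ between baseline and follow-up, after the four listed covariates are accounted for, is not in the documents and is shown as a range. SD means the residual SD of the outcome in the model with those four covariates.

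**Formulas.**

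- Adding baseline multiplies the residual variance by 1 − ρ².
- Detectable difference without baseline: (1.960 + 0.842) × √(2/96) = 2.802 × 0.1443 = 0.404 SD.
- Detectable difference with baseline: 0.404 × √(1 − ρ²).
- Power for a difference of 0.3 SD: Φ(0.3 / (√(1 − ρ²) × 0.1443) − 1.960). The 0.3 SD is illustrative.

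**Results, 96 per group.**

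| ρ (assumed) | Variance ratio 1 − ρ² | Detectable difference (SD) | Power for 0.3 SD |
|---|---|---|---|
| baseline left out | 1 | 0.404 | 54.7% |
| 0.3 | 0.91 | 0.386 | 58.7% |
| 0.5 | 0.75 | 0.350 | 67.0% |
| 0.7 | 0.51 | 0.289 | 82.9% |
| 0.8 | 0.36 | 0.243 | 93.4% |

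Put the other way round, leaving baseline out inflates the variance by 1/0.75 = 1.33 at ρ = 0.5 and by 1/0.51 = 1.96 at ρ = 0.7.

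**A side check on the 6-month visit.** For outcomes measured at both 6 and 12 months, I checked whether a joint model of the two visits would add much for the 12-month effect. Assume equal correlations between all visits, 96 patients per group seen at month 12, and 6 to 24 more per group seen at month 6 only. The partial correlation of the two follow-up values given baseline is (ρ − ρ²)/(1 − ρ²), which is 0.333 at ρ = 0.5 and 0.444 at ρ = 0.8. The variance factor is 1 − (partial correlation)² × (1 − 96/n₆), where n₆ is the number per group seen at month 6.

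- Smallest case (ρ = 0.5, n₆ = 102): 1 − 0.111 × 0.0588 = 0.9935, a gain of about 0.7%.
- Largest case (ρ = 0.8, n₆ = 120): 1 − 0.1975 × 0.20 = 0.9605, a gain of about 4%.

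Almost all of the available precision therefore comes from the baseline covariate.

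**The case against.** The strongest reply is that the text does not say baseline is excluded. The four names spell out what the balancing variables are; they do not declare that nothing else enters a model. The sentence also covers the Cox and logistic models, and a time-to-event outcome has no baseline value to list. For an outcome measured before and after treatment, many readers take analysis of covariance to mean adjustment for baseline. The authors may well have intended that.

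This stands as far as intent goes: the article is ambiguous and does not record a decision to leave baseline out. It does not remove the point. Four named covariates already make the model an ANCOVA, so the method's name does not supply the missing term. The article chose to state its adjustment variables, and a literal reading yields the less precise model.

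A reader might also infer that the 6- and 12-month values are analysed separately and that patients with missing visits are dropped. The article says neither. It gives no complete-case rule and states that "All analyses of the trial will use the intention-to-treat population, defined as all randomly assigned participants who received at least 1 dose of study medication". Spirometry and lung volumes have only one follow-up visit, so for them there is nothing to combine. The handling of repeated visits and missing values is commonly left to the full protocol or SAP, which is not shown, and its absence from an article is no fault.

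**Conclusion.** The point holds as a matter of specification and precision. The stated adjustment variables omit the baseline value of the outcome, and following the text literally would give wider confidence intervals than the collected data allow. The loss is small if the residual baseline-to-follow-up correlation is near 0.3 (variance ratio 0.91) and large if it is near 0.7 or 0.8 (0.51 or 0.36). These correlations are assumptions, and the true values will differ between outcomes.

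It would be wrong to read this as bias. Leaving out a baseline covariate does not in itself bias a randomised comparison, and nothing in the article shows that dropout would bias these analyses. Nor do the documents support requiring a repeated-measures model, given the gain of roughly 1 to 4% under the dropout patterns assumed above.

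Severity is low to moderate: the outcomes are secondary and labelled exploratory.

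**What to change.** In Statistical analysis, Secondary outcomes, state that each continuous outcome measured at t = 0 is analysed by ANCOVA with its baseline value as a covariate, in addition to study centre, gender, age and current smoking. If this was already intended, the same clause makes it explicit.

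The cost is a wording change made before the data are analysed. It needs no extra measurements, visits or patients, and it uses one degree of freedom per model.

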**Methods/Design:**

We will perform a randomised, multi-center, double-blind, placebo-controlled intervention study. The study population consists of 240 COPD patients aged 40 years and older with vitamin D deficiency (25-hydroxyvitamin D concentration < 50 nmol/L). Participants will be recruited after an exacerbation and will be randomly allocated in a 1:1 ratio to receive vitamin D3 16800 IU or placebo orally once a week during 1 year. Participants will receive a diary card to register the incidence of exacerbations and changes in medication during the study period. Visits will be performed at baseline, at 6 months and at 12 months after randomisation. Participants will undergo spirometry, measurement of total lung capacity and assessment of maximal respiratory mouth pressure. Several physical performance and hand grip strength tests will be performed, questionnaires on quality of life and physical activity will be filled in, a nasal secretion sample and swab will be obtained and blood samples will be taken. The primary outcome will be exacerbation rate.

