## Methods

### Study design and participants

The study is designed as a randomised double-blind, multi-center, placebo-controlled trial, with an intervention (*n* = 120) and a control group (*n* = 120). The study population consists of COPD patients with GOLD stages II-IV. Participants will be included if they have a vitamin D deficiency (25(OH)D concentrations <50 nmol/L) and a recent exacerbation of COPD. The eligibility criteria are described in Table 1. Participants will be recruited if they present with an exacerbation of COPD at the outpatient clinic or emergency ward. Screening serum 25(OH)D concentration will be measured during the exacerbation period. Inclusion and randomisation will take place 6–8 weeks after recruitment or at a later time point as soon as the participant has recovered. An exacerbation is defined as sustained worsening of respiratory symptoms during 48 h requiring oral corticosteroid, antibiotic or combination treatment that was initiated by a physician [38]. Convalescence is defined as recovery to the stable state. The recruitment will start in three academic hospitals and five peripheral hospitals in the surroundings of the academic centers. Study visits will be performed at baseline (t = 0), 6 months (t = 6) and 12 months (t = 12) after randomisation as depicted in Fig. 1. Participants will be contacted by telephone at 2, 4, 8 and 10 months The study is approved by the Medical Ethics Committee of the VU University Medical Center, Radboud University Medical Center and Leiden University Medical Center. Written informed consent will be obtained from all participants.

**Table 1 Tab1:** Eligibility criteria for the PRECOVID trial

Inclusion criteria	Exclusion criteria
Vitamin D deficiency (serum 25(OH)D < 50 nmol/l)	Severe vitamin D deficiency (serum 25(OH)D <15 nmol/l),
Postbronchodilator FEV_1_/FVC < 0.70, FEV_1_ < 80 % and diagnosis COPD confirmed by a physician	Use of a supplement containing more than 400 IU vitamin D per day
Recent COPD exacerbation	Use of maintenance dose oral corticosteroids
≥10 packyears of smoking	Diagnosed asthma
Age ≥ 40 years	Diagnosed osteoporosis
Written informed consent	Self-reported history of hypercalcaemia or nephrolithiasis
Ability to comply with all study requirements.	Self-reported presence of sarcoidosis
	Diagnosed chronic kidney disease stage 4 or higher (eGFR ≤ 29 ml/min/1.73 m2)
	Interfering malignant diseases
	Life expectation of less than 1 year on the basis of concurrent disease

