### Intervention

The participants will receive either vitamin D 16800 IU (3 tablets of 5600 IU) or a matching placebo (3 placebo tablets) orally once a week during 12 months in accordance with the randomisation. The study medication will be prepared under supervision of the clinical pharmacy of the VU University Medical Center. Participants will be asked to return the study medication that is left over and these tablets will be counted as a measure for compliance. Participants are allowed to use a maximum of 400 IU vitamin D a day during the study, as this is the recommended daily intake by the Dutch Health Council. Participants will be asked about their usual intake of dairy products. Participants are advised (according to the advice of the Dutch Health Council) to increase their intake to a level corresponding with 1000 mg calcium per day. If this is not feasible, it will be advised to use calcium supplements to a total calcium intake of 1000 mg/day during the study.

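### The per-protocol rule judges compliance by the 12-month serum 25(OH)D level, which the assigned treatment raises, so on placebo it does not measure tablet-taking

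*Protocol article*

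**What the plan says.** The last paragraph of the Statistical analysis section (Secondary outcomes) states: "A per-protocol analysis will be performed on those participants with a good compliance". It then equates that with "a good compliance i.e. obtaining a serum 25(OH)D concentration above the 20^th^ percentile after 12 months". Neither the arm to which the percentile belongs nor the arm to which the rule applies is given, so on its plain wording it covers participants in both.

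Three other statements bear on it:

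- Study design and participants: "Participants will be included if they have a vitamin D deficiency (25(OH)D concentrations <50 nmol/L" nmol/L. Both arms therefore start low.
- Intervention: participants take "vitamin D 16800 IU (3 tablets of 5600 IU) or a matching placebo (3 placebo tablets) orally once a week during 12 months". Only one arm is given a substance that raises the marker. Both arms may also use up to 400 IU of vitamin D a day of their own.
- Intervention, on leftover study medication: "these tablets will be counted as a measure for compliance". This count is not mentioned in the per-protocol definition.

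The main analysis set is stated separately: "All analyses of the trial will use the intention-to-treat population, defined as all randomly assigned participants who received at least 1 dose" of study medication. The per-protocol analysis is an addition to it.

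**The concern.** A per-protocol set is meant to keep those who took their assigned treatment, judged in the same way in each arm. Serum 25(OH)D at 12 months is measured after randomisation, and the active tablets are intended to change it. In the vitamin D arm a low value is at least partly a sign of missed tablets. In the placebo arm it reflects sun, diet, own supplements and general health, and says nothing about taking placebo tablets. One word, compliance, thus stands for two different things in the two arms.

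A percentile rule has a further weakness: it excludes a share fixed in advance, whatever the true compliance. If everyone took every tablet, a fifth of the reference group would still be labelled non-compliant.

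At stake is whether the per-protocol rate ratio can be read beside the intention-to-treat one. If low 25(OH)D goes with more exacerbations, which is the idea behind the trial, the rule selects on a risk factor, and it may do so unequally between the arms.

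**Working it through.** The article gives no figure for this rule, so there is none to reproduce. It also gives no 12-month 25(OH)D levels. Those below are assumptions, shown as ranges.

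**Inputs.** From the article: 1:1 allocation, 120 per arm, 20% dropout (so 120 × 0.8 = 96 per arm completing), cut at the 20th percentile. Assumed: normal 12-month levels, placebo mean 40-45 and SD 15-20, vitamin D mean 75-100 and SD 25-30 nmol/L.

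**1. Pooled percentile.** With equal arms, the shares dropped, p_P and p_A, satisfy (p_P + p_A)/2 = 0.20, so p_P + p_A = 0.40. If hardly any vitamin D patient falls below the cut-off, placebo must lose close to 40%. The cut-off c solves ½Φ((c − μ_P)/σ_P) + ½Φ((c − μ_A)/σ_A) = 0.20.

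| Placebo mean (SD) | Vitamin D mean (SD) | c | Placebo dropped | Vitamin D dropped |
|---|---|---|---|---|
| 40 (15) | 100 (25) | 36.0 | Φ(−0.27) = 39.5% | Φ(−2.56) = 0.5% |
| 45 (15) | 75 (30) | 37.0 | Φ(−0.53) = 29.7% | Φ(−1.27) = 10.3% |

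These two rows are the extremes of the assumed range. Of 96 per arm, they mean about 38 against 1 and about 29 against 10. If up to 20% of the vitamin D arm in the first row did not take the drug, the split would be about 33-40% against 0.5-7%. It is 20% against 20% only if treatment does not raise 25(OH)D.

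**2. The vitamin D arm's percentile used for everyone.** Here c = μ_A − 0.842σ_A.

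- 100 (25) against placebo 40 (15): c = 79.0, and Φ((79.0 − 40)/15) = 99.5% of placebo is dropped.
- 75 (30) against placebo 45 (20): c = 49.8, and Φ((49.8 − 45)/20) = 59.4% of placebo is dropped.

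**3. Within-arm percentiles.** Each arm loses 20% by construction. The numbers balance, but the placebo exclusions are unrelated to compliance.

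**4. Possible bias when the true rate ratio is 1.00.** Let the log exacerbation rate change by β per SD of 25(OH)D within arm, with β = −0.1, −0.2 or −0.3 (assumed). Among those kept (standardised level above k), the mean rate relative to the whole arm is m(k) = Φ(β − k)/Φ(−k). The per-protocol ratio is m(k_A)/m(k_P).

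- Pooled cut-off, first row above: k_P = −0.267 and k_A = −2.56. For β = −0.2, m(k_P) = 0.527/0.605 = 0.870 and m(k_A) = 0.991/0.995 = 0.996, so the ratio is 1.145. For β = −0.1 and −0.3 it is 1.067 and 1.235. A simulation of Poisson counts agrees (1.066, 1.144, 1.235).
- Pooled cut-off, second row above (less separation): 1.03, 1.07 and 1.10.
- Only the vitamin D arm trimmed at its own 20th percentile: k_A = −0.842, placebo untouched. For β = −0.2, Φ(0.642)/0.80 = 0.924. For β = −0.1 and −0.3 it is 0.964 and 0.882.
- Within-arm cut-offs: k is the same in both arms, so the ratio is 1.00 in this symmetric model.
- β = 0: 1.00 under every rule.

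**The case against.** The strongest reply is that little rests on this analysis. The primary analysis and the sample size do not use the per-protocol set, and no stated decision depends on it. That stands, and it limits the severity. A reader might infer that the trial's randomised comparison is broken; the article does not support that, because the intention-to-treat analysis is untouched.

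Other stronger readings are tempting and should not be drawn:

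- **That the bias is known to run toward no effect.** This holds only for a pooled cut-off and only if 25(OH)D predicts exacerbations. Trimming the vitamin D arm alone biases the other way. The section Vitamin D and COPD relates deficiency to disease severity, but it also reports cohort studies that found no relation between 25(OH)D and exacerbation rate, while noting their limited power. Without such a relation there is no bias in this model.
- **That the article contradicts itself on compliance.** The Intervention section calls the tablet count one measure of compliance, not the only one, and two measures can coexist. The fair point is that the measure which works alike in both arms is left out of the rule.
- **That the rule unmasks the analysts.** The article says "After the last participant finishes the trial masking will continue until after the data analyses". It does not say who handles the 25(OH)D values or when the set is formed, so this is speculation.
- **That everyone without a 12-month sample is removed.** Handling of missing values is not stated and may sit in the full protocol or analysis plan. Dropouts also trouble a tablet-count rule.

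The percentile's reference group may likewise be specified elsewhere. That would settle which problem arises, but not the basic one: under any reading that applies the rule to placebo, the level does not measure tablet-taking there. If the rule were meant for the vitamin D arm alone, which the text does not say, a selected active arm would face an unselected placebo arm.

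**Conclusion.** The rule is wrong as written and should be changed; severity is moderate. That a 25(OH)D level cannot show compliance with placebo follows from the design and needs no assumption. The exclusion percentages rest on assumed normal 12-month levels. The per-protocol ratios under no effect also rest on an assumed link between 25(OH)D and exacerbations: with the widest assumed separation, 1.07 to about 1.23 for a pooled cut-off (1.03 to 1.10 with less separation), and for any separation 0.96 to 0.88 if only the vitamin D arm is trimmed and about 1.00 for within-arm cut-offs. Bias is therefore possible, but neither its presence nor its direction is established.

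**What to change.** Replace the one sentence. Define the per-protocol set by the returned-tablet count that the Intervention section already collects, with a single threshold chosen in advance, applied identically in both arms and fixed before unmasking. State how participants who drop out and return no tablets are classified. Report achieved 25(OH)D at 12 months descriptively by arm rather than using it to select patients.

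The cost is small, since no new data are needed. The downsides are that tablet counts are an imperfect measure of adherence, and that patients who adhere may still differ from those who do not. The result therefore remains supplementary to the intention-to-treat analysis.
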